## Abstract

**Background:**

Mechanical insufflation-exsufflation (MI-E) is necessary for noninvasive management of respiratory clearance in patients with neuromuscular disorders (NMDs). Its utility has been proven, and the technique is recommended in a number of international guidelines for the management of patients with NMDs. However, the clearance of thick secretions adhering to the tracheobronchial walls could be problematic when these patients suffer from respiratory tract infections. To improve the effectiveness of the noninvasive technique, a novel device combining MI-E with high frequency oscillation (HFO) has been developed. However, the efficacy of HFO therapy in NMDs has not been well studied.

**Objective:**

The aim of this study was to elucidate the effect of MI-E combined with HFO for mucus removal in NMD patients. To evaluate its efficacy, changes in transcutaneous oxygen saturation (SpO_2_), which may predict intratracheal mucus removal, will be measured before and after use of MI-E.

**Methods:**

This is a single-center, nonblinded, nonrandomized prospective study that will enroll 5 subjects hospitalized in Kobe University Hospital owing to respiratory tract infection. All subjects will receive MI-E therapy a few times daily and will receive HFO every other day, for 6 days. Before and after MI-E use, SpO_2_ will be obtained and the change in SpO_2_ (ΔSpO_2_) between MI-E with and without HFO will be calculated. For every subject, the average of ΔSpO_2_ with or without HFO will be obtained and the null hypothesis that there is a mean change of 0 in the SpO_2_ between MI-E with and without HFO will be tested using the paired *t* test. If the treatment with HFO is found to be statistically significantly superior to the treatment without HFO, the study will conclude that HFO addition is more efficacious than no HFO addition.

**Results:**

A total of 2 subjects have already been recruited and enrolled in this study as of August 2018.

**Conclusions:**

This unique protocol will assess the efficacy of adding HFO to MI-E during the acute phase of respiratory tract infection in patients with NMDs.

**International Registered Report Identifier (IRRID):**

DERR1-10.2196/12102

## Introduction

### Background

Patients with neuromuscular disorders (NMDs) often have weak breathing muscles. As the disease progresses, vital capacity declines and the inability to expand and empty the chest fully results in reduced chest wall compliance [1-3]. As peak cough flow correlates with disease progression and lung capacity in patients with NMDs [4,5], insufficient coughing is problematic in patients with severe and advanced NMDs. Cough efficacy is related to clearance of secretions in the lung. Retention of intratracheal mucus leads to airway obstruction, causing increased work of breathing, decreased oxygenation, and ultimately respiratory failure [6]. Weak cough is thus a critical factor contributing to respiratory morbidity in NMD patients [7].

Therefore, coughing aids are necessary for patients with NMDs, and the use of assisted coughing techniques has been an important advance in the respiratory care of such patients, allowing intratracheal mucus to be controlled without the need for invasive methods, such as tracheostomy. Coughing aids include manually assisted and mechanically assisted aids [8]. Mechanical insufflation-exsufflation (MI-E) is performed using a device that generates positive pressure, provoking insufflation of the lung, and negative pressure, inducing exsufflation. A rapid change from positive to negative pressure generates air flow during exsufflation and facilitates the removal of intratracheal secretions [3,9].

It has been proven that MI-E helps to increase the peak cough flow, reduce the chance of hospitalization, permit a paradigm shift from invasive tubes to noninvasive management, and facilitate discharge to home [9-12]. Therefore, the use of MI-E is recommended in a number of international guidelines for the management of patients with NMDs [13-17].

Even if proper respiratory care is given, an inability to cough effectively and clear secretions puts patients with NMDs at risk of ventilatory failure during respiratory infection [18]. To improve the effectiveness of noninvasive techniques especially in cases of acute respiratory failure, a novel device that combines MI-E with high frequency oscillation (HFO) has been developed. During insufflation, exsufflation, or both phases, the device generates high-frequency oscillatory vibrations.

The application of HFO to the airway in patients with chronic obstructive pulmonary disease has been shown to change the viscoelastic properties of the secretions, making them more mobile [19]. Therefore, the addition of HFO to MI-E is expected to remove tenacious secretions in a noninvasive manner.

### Objectives

The aim of this study is to elucidate the effect of MI-E with HFO in terms of mucus removal in patients with NMDs. To evaluate the efficacy of the approach, changes in transcutaneous oxygen saturation (SpO_2_) and heart rate, and the subjective amount of mucus removed, are to be measured before and after use of MI-E, with and without HFO. The safety of the approach will also be evaluated by noting the frequency of adverse events and complications.

## Methods

### Study Design and Setting

This is a single-center, nonblinded, nonrandomized prospective study. As the use of oscillation is obvious, this study cannot be performed blindly. The study will be performed in the Department of Pediatrics, Kobe University Hospital, in Kobe, Japan. The study implementation period is from March 27, 2018, to January 31, 2022 (enrollment period: 3 years; follow-up period: 4 months from enrollment of the last subject).

### Eligibility Criteria

This study is conducted in patients who fulfill the following inclusion criteria and who do not meet any of the following exclusion criteria.

The inclusion criteria are as follows: patients with NMDs hospitalized in Kobe University Hospital owing to respiratory tract infection, who have already used MI-E without HFO or have started MI-E use in this study in addition to noninvasive ventilation, tracheostomy ventilation, and home oxygen therapy, and who provide written voluntary consent (or whose parents provide written voluntary consent) to participate in this study.

The exclusion criteria are as follows: patients with severe acute respiratory failure who have a very low SpO_2_ level (<90%) for more than 1 hour, albeit adequate ventilation or oxygen therapy; those who do not have tracheostomy and require intubation; those who refuse to participate in the study; and those for whom it is deemed inappropriate to participate in this study in the opinion of the investigator. These exclusion criteria are set to target patients with NMDs who have mild-to-moderate respiratory infection and to secure the safety of the subjects.

### Interventions

#### Description of Material

The Cough Assist E70 (Philips Respironics) is employed in this study. The device is used according to the manufacturer’s recommendation. The Cough Assist E70 is applied via an oronasal mask or the tracheostomy opening by trained parents, nurses, or doctors. It is used at least 3 times a day, as well as whenever SpO_2_ decreases, heart rate increases, or the patients have an increase in dyspnea or sense of retained secretions, in addition to the standard treatment, including oxygen supplementation and increased oxygen. It is set at 20 to 40 cm H_2_O for insufflation and −20 to −40 cm H_2_O for exsufflation pressure, with an insufflation and exsufflation time ratio of 1.5 to 2.5 and 0.8 to 1.5 seconds, respectively, and a pause of 0.5 to 2.0 seconds between each cycle. A total of 3 to 5 cycles are applied in every session. The frequency setting of oscillation is 15 Hz and the amplitude setting is 5 cm H_2_O. This oscillation frequency was derived from a similar previous study [20]. As a>5 cm H_2_O amplitude in the beginning of HFO use is not tolerated in child patients based on our clinical experience, 5 cm H_2_O is employed.

#### Description of the Processes and Interventions

The principal subinvestigator will obtain written informed assent or consent from patients or from their parents. After informed consent is obtained, the principal investigator or subinvestigator will determine the subject’s eligibility for enrollment. Enrollment should be done within 2 days after obtaining written consent, and protocol treatment should be started within 1 day after enrollment.

For the patients currently using MI-E, they will continue to use it with their existing settings. For new MI-E users, the setting described above will be used.

The following subject information will be recorded in the case report form (CRF) at the time of obtaining informed consent: date of informed consent; subject identification code; and subject’s baseline characteristics, including sex, birth date, height, body weight, medical history, concurrent diseases, and original setting of MI-E.

HFO will be added to MI-E in every subject on every other day, for 6 days. The addition of HFO on day 1 or day 2 will be determined in a random manner. When the subject is randomly selected to start the protocol with HFO on, the subject will receive MI-E with HFO treatment on days 1, 3, and 5 (Figure 1). If the subject is randomly selected to start the protocol with HFO off, they will receive MI-E with HFO on days 2, 4, and 6. The subject will thus be treated using MI-E with HFO for 3 days and without HFO for 3 days. During protocol treatment, the time for switching to HFO on and off has been set as 9 am.

**Figure 1 figure1:**
[figure not shown]
Outline of the study. Subjects will receive high frequency oscillation (HFO) every other day for 6 days. This shows the study schedule when the subject is randomized to start the protocol with HFO-on.

#### Criteria for Discontinuation

When continuation with the study is judged to be impossible for any of the following reasons, the principal investigator or subinvestigator will terminate the subject’s participation in the study and specify the date and time of discontinuation or dropout, reason for discontinuation, and clinical course in the medical records and CRF. The reasons for discontinuation include the following: when the subject or their parents request to withdraw from the study; when the subject’s respiratory status worsens and continuation of the study treatment is judged to be undesirable; when an adverse event, including pneumothorax, occurs and further continuation with the study is difficult; when the subject is discharged from the hospital; and when discontinuation from the study is appropriate for other reasons in the opinion of the principal investigator or subinvestigator.

When subjects who have already used MI-E have completed the protocol, MI-E will be set at the original setting. For subjects who commence use of MI-E for the first time in this study, MI-E will be set at a clinically favorable setting. HFO will be added if requested by the subject. For each subject, the observation period will end on the day when the subject visits the outpatient clinic of Kobe University Hospital for follow-up at 2 to 4 weeks after discharge.

### Outcomes

#### Primary Outcomes

Oxygenation change (SpO_2_) is the primary outcome in this study. Data will be obtained at every MI-E use during the study protocol. SpO_2_ values will be recorded at any point within 15 min before MI-E treatment and at 3 min after treatment.

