#### Statistical Analysis

This study will evaluate weather MI-E with HFO is significantly superior to MI-E without HFO in terms of the change in SpO_2_ as the primary endpoint of this study. If the protocol treatment with HFO is found to be statistically significantly superior to the treatment without HFO, the study will conclude that the addition of HFO to MI-E is more efficacious than not adding HFO.

The ΔSpO_2_ is calculated by subtracting the SpO_2_ value of pre-MI-E from the SpO_2_ value of post-MI-E. For every subject, the average of ΔSpO_2_ with or without HFO will be obtained. Then, a statistical analysis will be performed using a paired *t* test for the average ΔSpO_2_ values. The hypothesis testing will use a 2-sided significance level of 5%, with a calculation of the 2-sided 95% CI. The change in heart rate (ΔHR) as the secondary efficacy endpoint will be examined in the same way.

The safety endpoint of this study is the frequency of adverse events and complications. A summary table will be prepared for this endpoint. For estimation of the proportion, the exact 2-sided 95% CI for binomial distribution will be calculated by group. As necessary, Fisher exact test will be used for intergroup comparison. The final analysis will be performed after data from the subjects have been obtained and locked after the end of the follow-up period. The full analysis dataset and safety analysis dataset will consist of all subjects enrolled in this study, who performed at least one protocol treatment and for whom efficacy data are available.

The statistical analysis will be performed using GraphPad PRISM 7.02 (GraphPad Software).

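### The pre-treatment SpO2 may be read anywhere in a 15-minute window in an open-label study, which leaves ΔSpO2 and ΔHR open to observer choice and avoidable noise

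*Protocol article*

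**What the plan says.** Under Primary Outcomes: "SpO_2_ values will be recorded at any point within 15 min before MI-E treatment and at 3 min after treatment". The Statistical Analysis section defines the endpoint: "The ΔSpO_2_ is calculated by subtracting the SpO_2_ value of pre-MI-E from the SpO_2_ value of post-MI-E". It then reduces the sessions to one figure per subject and condition: "For every subject, the average of ΔSpO_2_ with or without HFO will be obtained". These averages are compared by a paired t test. The Secondary Outcomes section takes heart rate at the same times as SpO2, and ΔHR is analysed in the same way.

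Three other statements bear on how the pre value is obtained:

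- Study Design and Setting: "As the use of oscillation is obvious, this study cannot be performed blindly".
- Description of the Processes and Interventions: "During protocol treatment, the time for switching to HFO on and off has been set as 9 am". HFO alternates by day.
- Description of Material: "It is used at least 3 times a day, as well as whenever SpO_2_ decreases, heart rate increases", among other triggers. The same section says that the device is "applied via an oronasal mask or the tracheostomy opening by trained parents, nurses, or doctors".

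**The concern.** The two halves of the endpoint are not measured to the same standard. The post reading is tied to one moment; the pre reading may come from any moment in a quarter of an hour. Each point by which the pre value is lower raises ΔSpO2 by one point.

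Two features of the design make this matter. First, the condition is known before the pre value is taken, because HFO status is set for the day at 9 am and nobody is blinded. Second, in sessions started because SpO2 has dropped, the window can contain both the earlier stable value and the trough. Which one goes into the record then changes ΔSpO2 by the size of the drop.

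If the choice leans one way on HFO-on days and another on HFO-off days, part of the estimated HFO effect is an artefact of recording. If the choice has nothing to do with HFO, it adds variance to a comparison of only 5 subjects.

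**Working it through.** **Inputs from the article.** 5 subjects; 3 days per condition; at least 3 sessions a day. The article's own count of data points reproduces: 5 × 3 × 3 = 45 per condition, so at least 9 sessions per subject per condition. The test is a two-sided 5% paired t test on subject averages.

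**Assumptions.** The article gives no within-window variability. I take a within-window SD s of 1 to 2 SpO2 points and independent readings.

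**Step 1: how far the lowest of k readings falls below a typical one.** In SD units the expected drop e_k is:

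- k = 2: 1/√π = 0.56
- k = 3: 3/(2√π) = 0.85
- k = 5: 1.16 (by simulation)

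**Step 2: what reaches the HFO comparison.** Let f_on and f_off be the shares of HFO-on and HFO-off sessions in which the lowest of k readings is recorded. In the other sessions an arbitrary reading is recorded. The expected false difference in mean ΔSpO2 is

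B = s × e_k × (f_on − f_off).

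| Scenario | Calculation | B, points |
|---|---|---|
| Same choice on both days | f_on − f_off = 0 | 0 |
| Lowest of 3 in half of HFO-on sessions, none of HFO-off | (1 to 2) × 0.85 × 0.5 | about 0.4 to 0.85 |
| Lowest of 3 in all HFO-on sessions, none of HFO-off | (1 to 2) × 0.85 × 1 | about 0.85 to 1.7 |
| Lowest of 5 in all HFO-on sessions, none of HFO-off | (1 to 2) × 1.16 × 1 | 1.2 to 2.3 |

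Averaging over 9 or more sessions does not reduce B, because the choice is systematic.

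**Step 3: effect on the test.** This was simulated with no true HFO effect, 5 subjects, 9 sessions per condition and k = 3. Two further assumptions were a post-reading SD of 2 points and a between-subject SD of the HFO-on minus HFO-off difference of 0.5 to 1 point. Two-sided rejection rates at the 5% level:

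| Lowest of 3 recorded in | s = 1 | s = 2 |
|---|---|---|
| no session | about 5% | about 5% |
| half of HFO-on sessions | 8% to 10% | 15% to 18% |
| all HFO-on sessions | 18% to 25% | 43% to 56% |

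**Step 4: noise when the choice is unrelated to HFO.** The pre readings contribute s × √(2/9) = 0.47s to the SD of a subject's paired difference, that is 0.47 to 0.94 points. There is no expected shift. A single spot reading at a fixed moment would carry much the same variation unless its closeness to treatment makes it track the post value better. Averaging over a short interval is what can lower this term.

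**The case against.** A reader might infer that unblinded staff or parents will pick low pre values on HFO-on days and that the result will be biased by 1.2 to 2.3 points. The article does not support that.

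- It says who applies the device, not who records SpO2. An unblinded recorder is a reasonable inference from the open design and bedside use, and nothing contradicts it, but it remains an inference.
- It gives a time window for a recording. It does not say that several readings are taken and one selected. The Discussion mentions continuous SpO2 monitoring as a general justification for the outcome, not as this study's recording procedure.
- The largest figure needs five independent readings, the lowest taken in every HFO-on session, and no such choice on any HFO-off day. Readings minutes apart are likely to be correlated, which shrinks the drop. Any habit shared by both conditions cancels in the paired difference.
- Random timing error is averaged over at least 9 sessions per subject and condition.

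All of this stands, and it limits the size and certainty of the effect. It does not remove the point. One might add that recording details belong in the full protocol, but the article does not leave this matter open: it states the rule, gives the post reading an exact time and the pre reading a 15-minute range. Nothing else in the article narrows that range.

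**Conclusion.** The point holds as a weakness in how the primary measurement is fixed. The rule as written permits a pre value chosen with knowledge of the HFO condition, and it admits avoidable noise. ΔHR shares the weakness.

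The size is conditional. With within-window SDs of 1 to 2 points and independent readings, both assumed, the false HFO difference runs from 0 when readings are chosen alike on both days, through about 0.4 to 0.85 points under partial selection, to an upper bound of 1.2 to 2.3 points. Choice unrelated to HFO adds noise only. The documents show that bias is possible; they do not show that it has occurred or is likely, and the upper bound should not be quoted as an expected effect.

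**What to change.** Replace the open 15-minute window with one prespecified rule that is identical on HFO-on and HFO-off days and applies to both SpO2 and heart rate. The preferred rule is the monitor mean over the last minute before MI-E starts, read in the same way at 3 minutes after. A single reading immediately before the start would also remove the choice of reading, but would do less about noise.

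The cost is a change of wording in the protocol, the case report form and the recording instructions. Treatment is unaffected. The drawback is that 2 of the planned 5 subjects had been enrolled by August 2018, so up to 2/5 = 40% of the analysis set may rest on the old rule. Their sessions should be re-read from stored monitor data if such data exist, which the article does not say. Otherwise they should be flagged and examined in a sensitivity analysis. The new rule should begin with a new subject, not partway through a subject's 6 days, so that both conditions within each pair are measured alike.

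The change does not remove discretion over when an on-demand session starts. The report should acknowledge that as a remaining limitation.

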#### Secondary Outcomes

To evaluate the efficacy of the treatment, changes in heart rate will be obtained at the same time point used for SpO_2_. Additionally, the amount of mucus removed will be assessed subjectively, according to 3 grades (little, moderate, and abundant). As it was recommended by an external reviewer, peak cough flow was added to the secondary outcomes at the midpoint of the study. As safety end points, adverse events and the incidence of complications during the observation period will be obtained. The worst grade of the event will be considered the severity grade of each observed adverse event.

### Data Analysis Methods

#### Target Sample Size and Rationale

The primary endpoint of this study is the change in SpO_2_ (ΔSpO_2_) between MI-E with and without HFO. As no previous study has elucidated HFO efficacy in patients with NMDs, it is difficult to estimate how much change will be achieved. We assumed that the ratio of the average ΔSpO_2_ difference between HFO-on and HFO-off to the standard deviation would be about 1.1 to 1.2. To test the null hypothesis that there would be a mean change of 0 in the SpO_2_ between MI-E with and without HFO, using a paired *t* test with a 2-sided significance level of 5% and 80% power for the analysis of the primary endpoint, the required number of subjects was calculated to be 5. MI-E is applied more than 3 times a day, at least 45 data points are expected to be obtained from HFO-on or HFO-off. As the number of subjects enrolled per year can be assumed to be 1 to 2, the enrollment period has been set to 3 years.

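### Five subjects give about 47–53% power, not the stated 80%, at the plan's own effect size, two-sided 5% level and paired t test

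*Protocol article*

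**What the plan says.** All the inputs are in the protocol article, under Target Sample Size and Rationale:

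- **Effect size:** the authors assume that "the ratio of the average ΔSpO_2_ difference between HFO-on and HFO-off to the standard deviation would be about 1.1 to 1.2". They add that no earlier study gives a basis for an estimate.
- **Test, level and power:** the calculation is described as "using a paired *t* test with a 2-sided significance level of 5% and 80% power for the analysis of the primary endpoint".
- **Result:** "the required number of subjects was calculated to be 5".
- **Data yield:** "at least 45 data points are expected to be obtained from HFO-on or HFO-off".
- **Accrual:** "As the number of subjects enrolled per year can be assumed to be 1 to 2", over a three-year enrolment period.

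The Statistical Analysis section fixes the unit of analysis. It says "For every subject, the average of ΔSpO_2_ with or without HFO will be obtained", and then "a statistical analysis will be performed using a paired *t* test for the average ΔSpO_2_ values". It repeats the two-sided 5% level, plans a 95% CI, and makes statistical significance the condition for concluding that adding HFO is more efficacious.

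**The concern.** A paired t test on five subjects has 4 degrees of freedom and a critical value of 2.776. A standardised difference of 1.1 to 1.2 gives an expected test statistic of only about 2.5 to 2.7, below that critical value. Power near 80% is therefore implausible on sight, and 5 looks like the result of a formula that does not match the stated test.

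The stated power governs how the result will be read. A reader told that the trial has 80% power will take a non-significant result as fair evidence against an effect of the assumed size. If the true power is about one half, such a result says little. The stated decision rule rests on significance alone, so the error bears directly on the trial's conclusion.

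**Working it through.** **Inputs.** Ratio d = 1.1 to 1.2, two-sided alpha 0.05, target power 0.80 and n = 5 (Target Sample Size and Rationale); paired t test on one average per subject and condition (Statistical Analysis). The ratio is first read as mean difference over the SD of the within-subject differences, the natural meaning for a paired t test.

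**1. Trying to reproduce 5 with a normal approximation.** n = ((z_alpha + z_power) / d)².

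- Two-sided 5%: (1.960 + 0.842)² = 7.849. At d = 1.1, 7.849 / 1.21 = 6.49, so 7. At d = 1.2, 7.849 / 1.44 = 5.45, so 6. The same approximation puts power at n = 5 at 69.1% to 76.5%.
- One-sided 5%: (1.645 + 0.842)² gives n = 5.11 at d = 1.1, 4.67 at 1.15 and 4.29 at 1.2. This rounds up to 5 for ratios of about 1.11 and above.

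Of the one- and two-sided t and normal calculations tried with the stated ratio, only the one-sided normal formula gives 5. It contradicts both the stated two-sided level and the stated t test.

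**2. The stated test, computed exactly.** Power = P(T > t_crit) + P(T < −t_crit), where T is noncentral t with n − 1 degrees of freedom and noncentrality d√n. At n = 5, t_crit = 2.776 and the noncentrality is 1.1 × 2.236 = 2.46 up to 1.2 × 2.236 = 2.68.

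| n | d = 1.1 | d = 1.15 | d = 1.2 |
|---|---|---|---|
| 5 | 46.6% | 49.8% | 53.0% |
| 6 | 58.3% | 61.9% | 65.5% |
| 7 | 68.1% | 71.9% | 75.4% |
| 8 | 76.1% | 79.6% | 82.8% |
| 9 | 82.3% | 85.5% | 88.2% |

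Simulation with one million trials per effect size gives 46.7% and 53.1% at n = 5, which agrees. The smallest n reaching 80% is 9 at 1.1, 9 at 1.15 and 8 at 1.2. A one-sided 5% t test at n = 5 would still reach only 64.8% to 71.2%.

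**3. Effect needed for 80% power with 5 subjects.** Solving the same formula for d gives 1.68.

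**4. Observed effect needed for significance with 5 subjects.** The test statistic is the observed ratio × √5, so the observed ratio must exceed 2.776 / 2.236 = 1.24. A trial that observed exactly the planned 1.1 to 1.2 would not be significant.

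**5. The 45 session values.** 5 subjects × 3 days × 3 sessions = 45 per condition. They are averaged within subject before the test, which leaves 5 differences and 4 degrees of freedom. The test is run on these averages, so the ratio entering its power calculation already refers to them.

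**6. The other reading of the SD.** If the SD is that of a single condition (equal in both), the ratio for the paired test is d / √(2(1 − ρ)), with ρ the within-subject correlation. Power at n = 5 is then:

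- ρ = 0: 26.9% (d = 1.1) to 30.9% (d = 1.2)
- ρ = 0.5: 46.6% to 53.0%, the same as above
- 80% requires ρ = 1 − (d / 1.682)² / 2, which is 0.79 at d = 1.1 and 0.75 at d = 1.2

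**The case against.** The strongest objection is that the text says only "to the standard deviation would be about 1.1 to 1.2" and never says which SD is meant. If it is the single-condition SD, five subjects do give 80% power once the within-subject correlation is about 0.75 to 0.79. The 47–53% figure is therefore conditional on a reading. This stands as a caveat, but it does not rescue the plan: no correlation is stated, and at low correlation the same reading lowers power to 27–31%.

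It is also fair that the article does not offer the 45 data points as the justification for 5. They follow as an expected yield. The most that can be asked is that the text make clear they do not increase the sample size of the test.

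The article is candid in other respects. Its Discussion lists uncertainty about a sufficient sample size as the first limitation, its Conclusions call the study preliminary, a 95% CI is planned, and no conclusion is attached to a non-significant result. This reduces the harm. However, admitting that the effect is hard to guess differs from saying that 5 subjects are too few for the effect that was guessed, and the 80% claim carries no such qualification.

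Finally, 8 to 9 subjects do not fit the stated accrual: 1 to 2 per year for 3 years is 3 to 6. That is correct, and it favours correcting the power statement over raising the target.

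**Conclusion.** The concern holds. On the plan's own ratio, test and level, power with 5 subjects is 46.6% to 53.0%, and 80% needs 9 to 8 subjects. The shortfall is 4 to 3 subjects on a base of 5, too large for rounding to explain. The exact figures assume normally distributed within-subject differences and an SD that refers to those differences. Without that second assumption the conclusion becomes that 5 does not follow from the stated inputs unless an unstated correlation of about 0.75 to 0.79 is added. Either way, the sample size statement is wrong as written and must be corrected.

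**What to change.** Replace the power statement under Target Sample Size and Rationale with wording such as:

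*With 5 subjects, a paired t test at the two-sided 5% level has about 47–53% power if the mean within-subject difference is 1.1 to 1.2 times the standard deviation of the within-subject differences, and 80% power if that ratio is 1.68.*

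In the same section:

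- Name the SD. If the single-condition SD was intended, state the assumed correlation and recompute.
- State that session values are averaged within subject, so the test has 5 pairs whatever the number of sessions.
- Give feasibility as the reason for 5 subjects, if that was the reason. The accrual rate already given supports it.

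In Statistical Analysis, add that a non-significant result will be treated as inconclusive and that the estimate will be interpreted through its 95% CI, which is already planned. The superiority test can stay.

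If the 80% claim at 1.1 to 1.2 is kept, the number to print is 8 to 9; 9 is needed to cover the whole range. At 2 subjects per year that takes at least 4 years, against the 3 planned, so the enrolment period would have to change too.

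The recommended route costs only wording and a less favourable stated power. Recruitment, treatment schedule and test are unchanged. With 2 subjects enrolled as of August 2018, according to the article, the correction can be made well before the final analysis.
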